### 2.11. Status and Timeline of the Study

Participant recruitment commenced on 25 February 2025 and is currently ongoing. Recruitment is expected to be completed by 31 December 2028, and final data collection is anticipated by January 2029.

## 3. Discussion

Although FD is prevalent in KM clinics, prospective, real-world evidence remains limited. Although several multicenter studies have investigated FD, most have been explanatory RCTs focusing on standardized herbal formulas in controlled hospital settings [16,18]. To the best of our knowledge, this prospective observational cohort study is designed to provide valuable real-world evidence on the clinical outcomes and safety of individualized HDs administered in routine primary care.

Unlike traditional RCTs, this study adopts a pragmatic observational design that reflects routine clinical practice, in which treatment strategies are tailored to individual patients and often combined with other KM modalities. By prospectively collecting data from 23 primary KM clinics, this study is expected to provide clinically meaningful insights into current prescription patterns, treatment responses, and safety outcomes in routine clinical settings.

This study has several important policy implications. In South Korea, the national pilot program for health insurance coverage of HDs was recently expanded to include FD as a target condition [11]. Despite the widespread clinical use of HDs in the treatment of gastrointestinal disorders, prospective real-world evidence remains insufficient. Therefore, this study will generate valuable, hypothesis-generating data to support the ongoing national pilot program and inform future healthcare policies and clinical decision-making.

This study has several inherent methodological limitations. First, because this is an observational study without a randomized controlled group, a causal relationship between HD treatment and clinical outcomes cannot be established. Second, the inherent heterogeneity of individualized prescriptions and concomitant KM interventions may complicate the interpretation of the treatment effects. To address potential confounding and heterogeneity, multivariable regression analyses and exploratory subgroup analyses based on concomitant KM interventions will be performed. Third, the 4-week observation period may be insufficient to evaluate the long-term effectiveness and recurrence patterns of FD. Furthermore, loss to follow-up and missing data may occur due to pragmatic primary care factors, such as early symptom resolution, scheduling conflicts, or noncompliance. Finally, because the study relies primarily on patient-reported outcomes in an open-label setting, reporting and expectation biases cannot be excluded.

Despite these limitations, this study provides a practical, standardized framework for generating pragmatic real-world evidence on HD-based care for FD in primary KM settings. This study will serve as foundational, hypothesis-generating evidence to support future pragmatic clinical research and evidence-based healthcare policies integrating KM into public health systems.

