## Abstract

**Objective**: Functional dyspepsia (FD) is frequently treated in Korean Medicine (KM) clinics in South Korea. With the recent inclusion of herbal decoctions (HDs) for FD in the national pilot program for health insurance coverage, the generation of real-world evidence has become an important policy priority. In this study, we aim to evaluate the real-world clinical outcomes and safety of individualized HD-centered KM care in patients with FD in a primary care setting. **Methods**: This multicenter, prospective, single-arm observational cohort study will enroll 150 participants who meet the Rome IV criteria for FD across 23 KM clinics nationwide. Participants will receive individualized HDs, prescribed at the discretion of the attending physicians, as the primary treatment for 4 weeks. Concomitant KM treatments (e.g., acupuncture, moxibustion, and cupping) are permitted as clinically needed to preserve the pragmatic nature of routine care. The primary outcome is the change in the total symptom score on the Nepean Dyspepsia Index, Korean version (NDI-K), at week 4. Secondary outcomes include the Numeric Rating Scale for overall severity, overall treatment effect, and safety monitoring. Statistical analyses will be performed using mixed models for repeated measures to account for repeated observations and missing data. **Discussion**: This study will evaluate the pragmatic outcomes of individualized HD-centered KM care in routine clinical practice, thereby supporting the external validity of its findings. The findings are expected to provide foundational real-world data for the national HD pilot program, and these data may serve as a reference for healthcare policies and clinical decision-making. Clinical Trial Registration: Clinical Research Information Service (registration number KCT0010254); registered on 11 February 2025.

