In KM, FD is managed through individualized interventions, with herbal decoctions (HDs) serving as the core modality. Although various herbal medicines (HMs) have demonstrated clinical efficacy against FD in randomized controlled trials (RCTs) [8,9], these explanatory studies often have inherent limitations in their clinical applicability. Most existing RCTs have been conducted in highly controlled hospital-based settings with rigid inclusion criteria that do not fully account for the complexity of primary care. Specifically, the standardized protocols of traditional RCTs often overlook the individualized nature of KM, in which treatments are dynamically adjusted based on pattern identification (*Bian-Zheng*) and patient-centered factors [10]. Alternative designs such as pragmatic trials or cluster-randomized trials can provide comparative real-world evidence; however, they may still have limitations in fully reflecting the flexible, individualized nature of primary KM practice.

Recently, the South Korean government launched the second phase of a national pilot program to expand health insurance coverage, with FD newly included as a key target condition [11]. This policy shift underscores the need for high-quality real-world data on the utilization, clinical outcomes, and safety of HDs in routine practice. Given the individualized and multimodal nature of primary KM care, a multicenter prospective observational cohort study is well suited to capturing routine clinical outcomes. Therefore, this study aims to evaluate the real-world clinical outcomes and safety of individualized HD-centered KM care in patients with FD across 23 primary KM clinics. Although uncontrolled observational studies have inherent limitations—such as confounding, selection bias, and expectation bias—this study will generate valuable pragmatic evidence to support the ongoing national HD pilot program and offer practical insights for future health policy and clinical practice.

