### 2.4. Interventions

Because this is an observational study, no experimental intervention is assigned or controlled by the researchers. During the 4-week observation period, participants will receive individualized KM treatments, defined as “HD-centered care,” in which tailored HDs serve as the primary therapeutic modality, supplemented by routine individualized KM care as dictated by the attending physician.

Although HDs are flexibly individualized based on pattern identification, representative formulas frequently prescribed in primary care for FD include Banha-sasim-tang, Yukgunja-tang, and Hyangsa-pyeongwi-san [8,9,12]. These traditional formulas are well documented for improving gastrointestinal motility, modulating visceral hypersensitivity, and protecting the mucosal barrier through key bioactive compounds, and they have a well-established safety profile in clinical practice.

In principle, HDs are prescribed in standard dispensing units (typically comprising 20 therapeutic doses yielding 30 packs, designated for administration three times daily), though these may be adjusted according to individual clinical conditions and practice environments. Detailed prescriptions and dosage information—including repeated prescriptions—will be recorded, and patient adherence to HDs will be monitored based on patient-reported remaining pack counts during follow-up assessments.

Other KM treatments administered as part of routine care, such as herbal extract granules, acupuncture, electroacupuncture, moxibustion, cupping therapy, and pharmacopuncture, may also be provided at the treating physician’s discretion. Detailed information on all KM interventions and concomitant medications, including prescription duration, administration frequency, and concomitant treatments, will be thoroughly documented in the electronic case report form (eCRF) to capture treatment exposure and heterogeneity.

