#### 2.5.1. Primary Outcome Measure

The primary outcome is the change in the total symptom score of the Korean version of the Nepean Dyspepsia Index (NDI-K) from baseline to week 4. The NDI-K is a validated tool for quantifying the severity of dyspeptic symptoms and their impact on patient well-being. This study will use a 15-item symptom subscale that captures the frequency and intensity of discomfort; higher cumulative values represent a greater symptom burden [13]. As the original NDI comprises distinct symptom and quality-of-life subscales, this study specifically uses the 15-item Nepean Dyspepsia Symptom Index (NDSI) as the primary outcome measure to precisely evaluate core physical discomforts associated with FD, independent of general quality-of-life domains. In accordance with established clinical trial standards employing the NDSI [14], therapeutic efficacy will be evaluated primarily through continuous score reductions in this symptom subscale.

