To account for clinic-level clustering and intra-center correlations across the 23 participating clinics, participating sites will be included as a random effect in the mixed models. Furthermore, to accommodate potential confounding factors and treatment heterogeneity in routine clinical practice—such as baseline clinical characteristics, symptom severity, and concomitant KM interventions—multivariable regression models incorporating these key variables as covariates will be performed. Additionally, exploratory subgroup analyses based on these clinical factors may be conducted to evaluate their potential modifying effects. This approach effectively addresses within-subject correlations and handles missing data under the missing-at-random (MAR) assumption; consequently, no explicit data imputation is performed in the primary model. To test the robustness of the primary outcomes against potential departures from the MAR assumption (e.g., missing not at random), sensitivity analyses will be conducted using multiple imputation (MI) under MAR and pattern mixture models (PMMs) with delta-adjustment. Sensitivity analyses will also be conducted using the per-protocol set (PPS) to verify that the missing data pattern does not substantially alter the main findings. Additionally, paired *t*-tests will be performed as a supplementary analysis to evaluate overall within-subject pre- and post-treatment changes. Furthermore, potential assessment mode differences (in-person vs. telephone follow-up) will be evaluated by including assessment mode as a covariate or subgroup factor in secondary analytic models.

Safety monitoring data will be descriptively summarized, focusing on the frequency, intensity, and causal relationships of any recorded AEs. Exploratory subgroup analyses will also be performed based on whether participants received concomitant KM interventions. Where applicable, differences in the AE incidence rates between these subgroups will be evaluated using the chi-square test or Fisher’s exact test.

The full analysis set (FAS) will serve as the primary population for effectiveness outcomes, whereas the PPS and safety analysis set (SAS) will be used for per-protocol and safety evaluations, respectively. The specific criteria for these sets of analyses are outlined below.

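### Concomitant KM treatment received during follow-up serves as covariate, effect modifier and AE grouping factor; these secondary associations can be biased, and the adjustment cannot address confounding of the pre–post change

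*Protocol article*

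**What the plan says.** All references are to the protocol article.

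- **Design.** The Abstract states: "This multicenter, prospective, single-arm observational cohort study will enroll 150 participants". Section 2.10 requires at least one HD administration for both the full analysis set and the safety set, so there is no group without HD.
- **How add-ons are given.** According to the Abstract, concomitant KM treatments "are permitted as clinically needed to preserve the pragmatic nature of routine care". Section 2.4 says other KM treatments "may also be provided at the treating physician’s discretion". The Introduction describes KM as a practice in which "treatments are dynamically adjusted based on pattern identification".
- **When they are recorded.** Table 2 schedules the KM treatment record at Visits 1, 2 and 3 and at unscheduled visits.
- **How they are analysed.** Section 2.10 lists concomitant KM beside baseline characteristics and symptom severity, and says "multivariable regression models incorporating these key variables as covariates will be performed". It allows subgroup analyses of effect modification by the same factors. It also splits participants by whether they received concomitant KM, with no time window, and says that where applicable "differences in the AE incidence rates between these subgroups will be evaluated using the chi-square test" or Fisher's exact test.
- **Why.** The limitations paragraph of the Discussion: "To address potential confounding and heterogeneity, multivariable regression analyses and exploratory subgroup analyses based on concomitant KM interventions will be performed".
- **Related wording.** Section 2.5.1: "therapeutic efficacy will be evaluated primarily through continuous score reductions in this symptom subscale".
- **Primary model.** Section 2.10 fits visit, baseline NDI-K and their interaction, with site as a random effect. Concomitant KM is not in it.

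**The concern.** Two different problems meet in one variable.

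First, having received an add-on by week 4 is not a baseline characteristic. A physician who adds treatment as needed may do so because the patient is doing badly, or because of an AE. A patient who stays longer or attends more often has more occasions to receive one. The coefficient or subgroup difference then mixes any effect of the add-on with the reasons for giving it. An inert add-on could look harmful, and AE incidence could look linked to it merely through contact time.

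Second, the stated purpose does not fit the design. With all analysed participants on HD there is no HD contrast to adjust, so no covariate can take natural course, regression to the mean or expectation out of the mean change. A reader of the Discussion could believe that these regressions deal with that limitation. The results are meant to inform an insurance pilot programme, where associations by modality may be read as evidence about modalities.

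**Working it through.** **1. The plan's own figures (Section 2.9).** Inputs: 150 enrolled, 25% dropout, SD of change 10–12.

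- Evaluable: 150 × 0.75 = 112.5, stated as about 112.
- Margin for one mean: 1.96 × 10/√112 = 1.85 and 1.96 × 12/√112 = 2.22. Both reproduce.

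These margins are for the whole-cohort mean. If the cohort splits evenly (an assumption), a difference between two subgroups of 56 at SD 11 has margin 1.96 × 11 × √(2/56) = 4.07 points. That is the yardstick for the subgroup comparisons.

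**2. Timing.** Discretionary treatment over 4 weeks (Section 2.4), recorded up to Visit 3 and at unscheduled visits (Table 2), is grouped by receipt without a window (Section 2.10). Followed as written, an add-on started after a poor week-2 score, or after an AE, counts the same as one chosen at Visit 1.

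**3. What adjustment does to the pre–post change.** Write the mean change as HD effect + natural course + regression to the mean + expectation. All four terms are present in every participant. In least squares with mean-centred covariates the intercept equals the raw mean change, so adjustment leaves the sum as it is. With an uncentred yes/no add-on variable, the intercept becomes the fitted change in those without an add-on, which is a selected subset if uptake follows response.

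**4. Closed-form illustration.** Assumptions, none from the document: true add-on effect zero; 70% of those below the median week-2 improvement and 30% of those above it receive an add-on; correlation of week-2 and week-4 change 0.6; SD 11.

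- Mean standardised improvement in each half: ±0.798.
- Add-on group: 0.7 × (−0.798) + 0.3 × 0.798 = −0.319. No add-on: +0.319. Difference: 0.638 SD.
- Spurious week-4 difference: 0.638 × 0.6 × 11 = 4.2 points, about one 56-versus-56 margin.

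**5. Range by simulation.** 112 participants, 2,000 runs per cell, true add-on effect zero, mean change −10, least squares of week-4 change on baseline and add-on received (yes/no). Uptake is logistic in interim response, with log-odds rising by k per SD of poorer response. SD is from Section 2.9; k, the correlation and the mean change are assumed. Cells give the apparent harm in NDI-K points and the share of runs with p < 0.05 (two-sided).

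| SD | Correlation | k = 0 | k = 0.5 | k = 1 | k = 2 |
|---|---|---|---|---|---|
| 10 | 0.4 | 0.0 (4.5%) | 1.9 (16%) | 3.3 (42%) | 4.9 (74%) |
| 10 | 0.6 | 0.0 (4.9%) | 2.9 (32%) | 4.9 (75%) | 7.2 (98%) |
| 12 | 0.4 | 0.0 (5.1%) | 2.2 (17%) | 4.0 (42%) | 5.7 (74%) |
| 12 | 0.6 | 0.0 (4.5%) | 3.4 (32%) | 6.0 (77%) | 8.6 (98%) |

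In all cells the unadjusted mean change stays near −10. For k above 0, the adjusted change in those without an add-on moves to between −10.9 and −14.3, with nothing in the treatment having changed.

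**6. AEs.** No figure can be derived, but the structure is clear. Table 2 records both KM treatment and AEs at unscheduled visits, so more contact can raise both counts. The Discussion expects some loss to follow-up through early symptom resolution, which shortens the time for both. Nothing requires the add-on to precede the AE.

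**The case against.** The strongest reply is that little depends on these analyses. The primary model leaves concomitant KM out. Section 2.9 calls the study exploratory, the subgroup analyses carry the same label, and those on effect modification are only optional. The Discussion says that no causal relationship can be established and calls the data hypothesis-generating. All of this stands and limits the severity. It does not repair the analyses, because an exploratory label does not remove a bias that comes from how the variable is defined.

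Several stronger readings are tempting, and the documents do not support them:

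- *Add-ons are given when response is poor.* The text says only that they follow clinical need and discretion. They may largely start at Visit 1, in which case the response-driven bias would be small. If physicians added treatment for those doing well, the sign would reverse.
- *The spurious difference is twice the plan's margin of error.* That sets a two-group difference against a one-sample margin. Against the matching margin of about 4.1, the 4.2-point illustration is about one margin.
- *Conventional medication has been left out.* The covariate list in Section 2.10 is introduced as examples and includes baseline clinical characteristics, and Section 2.6.2 collects concomitant medication at baseline. A final covariate list may reasonably sit in another document.
- *There is no contrast at all.* There is one, with versus without add-on, and the models can legitimately describe heterogeneity. What is missing is an HD contrast.

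It is also fair to say that the definition of receipt could be settled in an analysis plan. The point remains because the article already fixes the uses of the variable and states a purpose that they cannot serve.

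**Conclusion.** The concern holds for the secondary and exploratory analyses only. As written, Section 2.10 conditions on a variable that can follow response or an AE, and the Discussion offers this as a way to address confounding when no HD comparator exists. The primary week-4 estimate is not affected, and a reader should not infer that it is.

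The size is unknown. With uptake log-odds of 0.5 to 2 per SD of poorer response and correlations of 0.4 to 0.6, an inert add-on appears about 2 to 9 points worse. With uptake independent of response there is no bias. That the AE comparison can be distorted follows from the recording schedule, but its direction and size cannot be given. The finding is an inexpensive improvement that should be made, not a flaw in the main result.

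**What to change.** 1. **Section 2.10, covariates and subgroups.** Define concomitant KM from the Visit 1 treatment record only. Describe later add-ons (type, timing, frequency) without entering them as predictors of week-4 change. The Visit 1 variable still reflects indication, so its coefficient is a prognostic description, but later response cannot have caused it.
2. **Section 2.10, AEs.** Report AEs by concomitant KM descriptively, with onset relative to the start of the modality and with follow-up time shown for both groups. Do not read the chi-square or Fisher's exact test as a comparison of risk; it is best left out.
3. **Wording.** In the Discussion, state the purpose as describing heterogeneity and baseline predictors of change, not addressing confounding. In Section 2.5.1, replace therapeutic efficacy with symptom change.

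A week-2 landmark model for later add-ons is less attractive than it looks. With the ±7-day windows in Table 2, Visit 2 (14 + 7) and Visit 3 (28 − 7) can both fall on day 21.

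**Cost.** Table 2 already schedules the Visit 1 record, and Section 2.7 already records AE onset. The AE table needs a rule for when each modality is taken to have started. Later add-ons go unmodelled and an exploratory p-value is lost. Recruitment is expected to run until 31 December 2028 (Section 2.11), so the change can be made well before analysis.

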## Figures and Tables

**Table 1 healthcare-14-02439-t001:** Eligibility criteria.

**Inclusion Criteria**
Adults aged 19–74 years. Patients diagnosed with FD according to the Rome IV criteria, presenting with at least one symptom (postprandial fullness, early satiation, epigastric pain, or epigastric burning) that started at least 6 months prior and persisted for the last 3 months, without structural findings explaining the symptoms, as confirmed by upper gastrointestinal endoscopy performed after symptom onset. Patients who voluntarily provide written informed consent using a form approved by the Institutional Review Board (IRB).
**Exclusion Criteria**
Organic diseases (e.g., peptic ulcer, gastroesophageal malignancy, or pancreaticobiliary disease) identified by endoscopy or other diagnostic tests performed after symptom onset. History of major gastrointestinal surgery (excluding appendectomy > 6 months prior). Presence of alarm symptoms (e.g., unexplained weight loss, hematochezia, dysphagia, or persistent vomiting). Severe underlying pathologies affecting the cardiac, pulmonary, hepatic, or renal systems. Significant neuropsychiatric history (e.g., major depressive disorder or schizophrenia). Pregnant or lactating women. History of drug or alcohol abuse. Participation in other clinical trials that may interfere with this study.

**Table 2 healthcare-14-02439-t002:** Participant timeline: Schedule of enrollment and assessments.

	STUDY PERIOD				
TIMEPOINT (Week ± Day)	SCREENING (~1 week)	Visit 1 (0)	Visit 2 (2 weeks ± 7 days)	Visit 3 (4 weeks ± 7 days)	Unscheduled Visit
